**Participant information and informed consent**

The investigator must explain the nature of the study to each trial participant, its purpose, the procedures involved, the expected duration, the potential risks, benefits involved, and any discomfort it may entail. Each trial participant must be informed that participation in the study is voluntary and that they may withdraw from the study at any time, and that withdrawal of consent will not affect their subsequent medical treatment or relationship with the treating physician. The participant should be provided with enough time to think about their participation in the study without any pressure.

The Informed Consent should be given by means of a standard written statement (please refer to the appendix). The trial subject should read the statement and consider their decision before signing and dating the document and should be given a copy of the signed document. No participant can enter the study before his/her Informed Consent has been obtained. No study-related procedures will be performed before Informed Consent is obtained. If written consent is for some reason not possible, oral consent can be obtained if witnessed by a signed statement from one or more persons not involved in the study, mentioning why the participant was unable to sign the form.

**Withdrawal of informed consent**

Participants may withdraw their consent to participate at any time of the trial without providing its reason. Nevertheless, the participant should be asked for the reason for the premature termination after being informed that they do not need to answer this question. The participant must be informed that choosing not to participate or to withdraw the consent will not affect their subsequent treatment or relationship with the study group. The date of enrolment and reason for withdrawal is to be documented in any case. The participant is to be informed that in case of revocation of their consent, the stored data may be used further, as may be necessary:

• to assess effects of the study intervention to be tested

• to guarantee that the interests of the participant are not impaired

• to comply with the regulatory requirements

**Enrolment and randomisation**

Randomization and allocation concealment: 1) Assign numbers to eligible participants who meet the inclusion criteria and do not meet any exclusion criteria; 2) Generate random numbers: An individual not involved in the intervention uses SPSS 26 software to sequentially generate 10 random numbers; 3) Number the participants in order and match them with the generated random numbers; 4) Group participants based on the matching results (the method is: sort the 10 random numbers from smallest to largest to obtain sequence numbers R, with R1–R5 designated for the group starting with MICT followed by HIIT, and R6–R10 for the group starting with HIIT followed by MICT), and place the group information into envelopes; 5) Give each newly enrolled participant the corresponding envelope containing group information in sequence, and directly enter the predetermined group to start the experiment. The above grouping operations are performed by individuals not involved in the intervention.

**Violation of eligibility criteria**

If for any reason, a participant who would have been included in the study turns out to have violated the eligibility criteria, investigators shall proceed as follows. In the case that this participant has not been randomised, immediately stop their participation in the entire trial. Since by this time, an ID code has been assigned to the participant, notify in the participant list that the participant has been withdrawn. Do not use this ID code for any other participant. If the participant has already been randomised, contact the lead investigators immediately. In general, the violation of eligibility criteria is not a reason for the premature withdrawal of the participant from the study. Stop the study participation immediately only in case the violated criteria represent an additional risk for the participant or in case the participant has been randomised by an error without his/her consent. In all other cases, proceed per the protocol and wait for instructions coming from the coordinating investigators.

**Adverse event (AE/SAE)**

**Adverse event (AE)**

An event that is an unfavourable or unintended sign, symptom, or disease associated with exercise training.

**Serious adverse event (SAE)**

Any long-term or temporary life-threatening condition associated with exercise training. These conditions mean any adverse experience that results in any of the following outcomes: death, inpatient hospitalisation (within 24 hours of last training session), persistent or significant disability/incapacity.

**Response to AEs**

In the case of an AE, the coordinating investigator MUST be notified within 24 hours, filing and submitting an SAE report via email to the investigators.

**Analysis of safety**

All AEs as part of the screening, baseline, or during the training period should be reported. In the context of this study, after baseline testing, AEs are those which could take place during the exercise intervention. Hence, it is mandatory to record and document all, which occur after the start and no later than two hours after the end of the exercise. The frequency of adverse events related to the exercise will be monitored. If required, the study protocol may be amended in terms of individual training dosage.

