| Blinding | #11a | If done, who was blinded after assignment to interventions (for example, participants, care providers, those assessing outcomes) and how. | sDocument 1. 17–18 |
| Blinding | #11b | If relevant, description of the similarity of interventions | sDocument 1. 17–18 |
| Statistical methods | #12a | Statistical methods used to compare groups for primary and secondary outcomes | 11–12 |
| Statistical methods | #12b | Methods for additional analyses, such as subgroup analyses and adjusted analyses | 11–12 |
| **Results** |  |  |  |
| Participant flow diagram (strongly recommended) | #13a | For each group, the numbers of participants who were randomly assigned, received intended treatment, and were analysed for the primary outcome | 12 |
| Participant flow | #13b | For each group, losses and exclusions after randomization, together with reason | sDocument 4. 8 |
| Recruitment | #14a | Dates defining the periods of recruitment and follow-up | 7 |
| Recruitment | #14b | Why the trial ended or was stopped | NA |
| Baseline data | #15 | A table showing baseline demographic and clinical characteristics for each group | sDocument 4.  2–3 |
| Numbers analysed | #16 | For each group, number of participants (denominator) included in each analysis and whether the analysis was by original assigned groups | sDocument 4.  8 |
| Outcomes and estimation | #17a | For each primary and secondary outcome, results for each group, and the estimated effect size and its precision (such as 95% confidence interval) | 12–14 |
| Outcomes and estimation | #17b | For binary outcomes, presentation of both absolute and relative effect sizes is recommended | NA |
| Ancillary analyses | #18 | Results of any other analyses performed, including subgroup analyses and adjusted analyses, distinguishing pre-specified from exploratory | 12–14 |
| Harms | #19 | All important harms or unintended effects in each group (For specific guidance see CONSORT for harms) | NA |
| **Discussion** |  |  |  |
| Limitations | #20 | Trial limitations, addressing sources of potential bias, imprecision, and, if relevant, multiplicity of analyses | 22 |
| Generalisability | #21 | Generalisability (external validity, applicability) of the trial findings | 19 |
| Interpretation | #22 | Interpretation consistent with results, balancing benefits and harms, and considering other relevant evidence | 20–22 |
| Registration | #23 | Registration number and name of trial registry | Cover letter |

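### Mandatory adverse event recording stops two hours after exercise, so an event with later onset can meet the protocol's own SAE definition yet fall outside the recording rule

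*Protocol*

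**What the plan says.** Three neighbouring parts of section 5 of the protocol bear on this.

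- **Serious adverse event (SAE).** A condition associated with exercise training is serious if it results in death, in "inpatient hospitalisation (within 24 hours of last training session"), or in "persistent or significant disability/incapacity". Only hospitalisation carries a time limit.
- **Response to AEs.** "In the case of an AE, the coordinating investigator MUST be notified within 24 hours, filing and submitting an SAE report". The heading and the opening words concern any AE, but the form to be filed is the one for serious events.
- **Analysis of safety.** The section opens broadly: "All AEs as part of the screening, baseline, or during the training period should be reported". It then narrows: "after baseline testing, AEs are those which could take place during the exercise intervention". From that it concludes that investigators must "record and document all, which occur after the start and no later than two hours after the end of the exercise". It adds that the frequency of exercise-related adverse events will be monitored and that the protocol may be amended in response. It gives no separate or longer window for serious events.

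On timing, Table 1 ends with Visit 3 in week 6. In Table 2 the last time point is T5C, 15 minutes after the second session. Table 2 has no adverse event item at any time point.

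**The concern.** The collection rule should be at least as wide as the definition of what has to be caught. Here the definition of a serious event extends beyond the recording rule, and no other section extends the rule. A site that followed the text exactly could leave an event unrecorded that the same protocol classes as serious.

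What is at stake is the meaning of the safety data. The protocol intends to monitor adverse event frequency, and its Monitoring section lists safety aspects among the key data for source verification. If mandatory recording ends at two hours, a count of zero under either exercise mode is firm only for events that began by then. The trial has no safety endpoint, and neither the sample size nor the proteomic comparison depends on this rule.

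**Working it through.** The protocol states no figure to reproduce. The check sets the two rules side by side.

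**Inputs**

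- Recording rule (Analysis of safety): the event must occur between the start of exercise and two hours after its end. This clock runs on the onset of the event.
- SAE rule (Serious adverse event): admission within 24 hours of the last session, or death, or persistent or significant disability. This clock runs on the outcome.
- Notification rule (Response to AEs): 24 hours to inform the coordinating investigator. This is a deadline for passing on an event already known and does not lengthen collection.

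**Cases, for an event associated with the exercise**

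| Onset | Outcome | SAE by definition? | Recording mandatory? |
| --- | --- | --- | --- |
| During exercise or up to 2 h after | Admission within 24 h | Yes | Yes |
| More than 2 h after | Admission within 24 h | Yes | No |
| More than 2 h after | Death or lasting disability, at any time | Yes | No |
| More than 2 h after | None of the listed outcomes | No | No |

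The second and third rows are the contradiction. The first row shows that late admission alone is not the problem: if the event began within two hours, both rules apply and agree.

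**Does another provision cover those two rows?**

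1. *The opening sentence of Analysis of safety.* Read alone, it might cover the whole training period. The next two sentences restrict post-baseline events to those that could arise during exercise and then derive the two-hour rule from that restriction. It does not clearly close the gap. Even on a wide reading, a training period that ends with the second session gives nothing afterwards.
2. *After the first session.* Participants who continue return at Visit 3, two weeks later. New illness and serious safety issues are dropout criteria, and premature termination must be documented with date, circumstances and reason. A late event may surface by these routes, although neither table lists an adverse event enquiry at Visit 3.
3. *After the second session.* Neither table schedules a contact after T5C. The Participant timeline gives a duration of three months per participant, but no assessment is placed after week 6. A late event here has no planned route into the data.

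**AE and SAE reporting.** The Response to AEs section asks for an SAE report for any AE. Taken literally, this removes the distinction drawn by the two definitions just above it. The error runs towards over-reporting, so it is a separate drafting fault and not a cause of missed events.

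**The case against.** The strongest reply is that the two windows measure different things. One limits onset and the other limits an outcome, so a reader may wrongly infer that any hospitalisation ten hours after exercise escapes recording. It does not if the event began within two hours. This part of the reply stands, and the point is confined to onset after two hours.

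Other stronger readings are tempting and also fail:

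- *That most serious events would be missed.* One can subtract 2 from 24 and say that 22 of 24 hours, or 92%, are uncovered. That sets an onset window against an outcome window and counts clock hours. The documents say nothing about when events occur, and they do not say whether the 24 hours run from the start or the end of a session. The figure does not measure missed events.
- *That all 20 sessions (10 participants × 2) are equally exposed.* After the first session there are the indirect routes described above. The plainly uncovered sessions are the second ones, at most 10.
- *That the protocol forbids later recording.* The two-hour sentence sets what is mandatory. An investigator may record more.
- *That the NA against harms in the CONSORT checklist shows that harms will be ignored.* That column holds page references for a report. It is not a rule on collection and does not contradict the safety section.

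It can also be said that the window is the same for both modes, that there is no safety endpoint, and that with 10 participants the number of late serious events may be zero. All of this is correct and limits the consequence. It does not remove the conflict between the definition and the recording rule.

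**Conclusion.** The concern holds for events with onset more than two hours after the end of exercise. Such an event can be an SAE under the protocol's definition while lying outside its mandatory recording rule. This is a conflict between stated rules, not detail left to another document.

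Its size cannot be put as a number of events, since the documents give no event rates or timings. In terms of coverage, the gap is clearest after the second session, for up to 10 participants, and partly mitigated after the first. The conclusion assumes that the two-hour sentence governs over the broader opening sentence, which is the natural reading because it is presented as following from the restriction just before it. If the broad sentence were meant to govern, the section would contradict itself and would still need rewording.

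The fault affects the safety data and the planned monitoring of adverse event frequency. It should be corrected because the correction is cheap. The sample size and the primary proteomic analysis are unaffected.

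**What to change.** 1. Reconcile the Serious adverse event, Response to AEs and Analysis of safety sections so that the mandatory recording period covers at least every event the SAE definition counts. State whether the 24 hours run from the start or the end of the session.
2. Give the rule a means of collection: for example, an adverse event question at Visit 3, covering the time since the first session, and one brief contact after the second session. Add both to Tables 1 and 2.
3. Reword the opening sentence of Analysis of safety so that it agrees with the sentences after it.
4. In Response to AEs, state separately what is filed for an AE and what is filed for an SAE.

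The cost is a wording amendment and about one short question or contact per session: up to 10 questions at a visit that already takes place and up to 10 brief contacts afterwards. No change to the interventions, the blood sampling or the proteomic analysis is needed.

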# ETHICAL AND LEGAL ASPECTS

## Ethical approval

This trial has been rigorously reviewed and approved by the Ethics Committee of Xiangya Hospital, Central South University, ensuring adherence to the ethical standards of the 1964 Declaration of Helsinki and its later amendments. This Randomized Crossover Trial (approval number 2023030379, registered at Chictr.org.cn under ChiCTR2300071797). The Involved participants will be asked to provided informed consent.

## Confidentiality

All participant information will be stored without their names or personal identification, or any other information which may reveal their identity. A special code will attach results and samples to a list of names.

## Others

**Participant information and informed consent**

Written and informed consent will be given, signed, and retrieved from all subjects at the beginning of the study, along with information sheets. The letter of informed consent will be provided to the participants in their native language (Chinese) and in terms understandable for the participants, followed by explanations from the investigators that should be clear to all participants. From there, participants will be afforded the right to:

- - To know that participation is voluntary
  - To withdraw themselves from the project at any time
  - To be given time to ask questions freely and receive answers before making a decision
  - To know of any benefits involved in participation
  - To know the degree of risk and burden involved in participation
  - To know the procedures that will be implemented in the case of incidental findings
  - To receive assurances that appropriate insurance cover is in place
  - To know how their data will be collected, protected during the project, and either destroyed or re-used at the end of the research; if plans to re-use the data exist, participants should be duly informed and also consented for this further usage
  - To know of any potential commercial exploitation of the research.

**Tests and associated risks**

If the participants fulfil the inclusion criteria and do not meet any condition that would exclude them from the study, we will perform several tests on each subject: cardiopulmonary exercise with cycle ergometry, assessments of measures of height, weight, waist:hip-ratio, in addition to health-related questionnaires. These tests will be performed before the training period. After testing, participants will be randomised to an exercise group or to a control group receiving modern advice.

Although the risk of an adverse event or serious adverse events is elevated during exercise compared to rest, this absolute increase of risk is low, and it is generally accepted that the benefits brought about by exercise outweigh the low-risk of adverse events. The cardiopulmonary exercise tests are aborted when the participant can no longer sustain or increase the exercise load, or by signs of ischemia and are undertaken with the supervision of clinicians. We recently published an article finding that cardiopulmonary exercise testing is a relatively safe form of testing in Chinese patients. The team has good experience in undertaking cardiopulmonary exercise testing and risk management.

**Advantages for participants**

In this project, each participant will receive a community-based circuit training program focused on improving different aspects of fitness, and hopefully improving cardiovascular health by decreasing several of the participant’s cardiovascular risk factors.

Regarding this research, there are no principal ethical concerns on physical exercise and conditioning, as these activities will improve cardiovascular and general health. Reduced exercise capacity and functionality as a consequence of inactivity is an important trigger of reduced quality of life, invalidity, and premature death. Therefore, any reduction of inactivity in adult population would be a benefit to general health.

**Adherence to the protocol**

This trial will be conducted in accordance with the laws of The People’s Republic of China and the ICH guidelines for Good Clinical Practice (GCP), taking into account the Declaration of Helsinki and all its revisions.

We define protocol violations as any deviations from the procedures outlined in this document, which may include:

• missed evaluations/ incorrect timing of evaluations

• non-compliance with the study intervention

It is the investigator's responsibility to make a reasonable effort to correct any protocol violation once the participant has been enrolled, in order to keep the subject in the study.

Major protocol violations must be immediately reported to the principal coordinating investigators during the study. All protocol violations will be listed and discussed in a roundtable led by the principal investigator and the nature of these violations will be defined.

Under the fast-paced working environment, however, it is possible that some minor variations could occur due to circumstances outside of the investigators' control. All such deviations will be documented in records, together with the reason for their occurrence, and where appropriate, detailed in the study report. The investigator makes every effort to record data according to the protocol.

**Dissemination Plan**

The results of this study will be disseminated to all participants who have taken part in the research via sharing the findings on the social media platforms.

# CONSORT Checklist

|  |  | Reporting Item | Page Number |
| --- | --- | --- | --- |
| **Title and Abstract** |  |  |  |
| Title | #1a | Identification as a randomized trial in the title. | 1 |
| Abstract | #1b | Structured summary of trial design, methods, results, and conclusions | 2-4 |
| **Introduction** |  |  |  |
| Background and objectives | #2a | Scientific background and explanation of rationale | 5-6 |
| Background and objectives | #2b | Specific objectives or hypothesis | 6 |
| **Methods** |  |  |  |
| Trial design | #3a | Description of trial design (such as parallel, factorial) including allocation ratio. | 7 |
| Trial design | #3b | Important changes to methods after trial commencement (such as eligibility criteria), with reasons | NA |
| Participants | #4a | Eligibility criteria for participants | sDocument 1. 12-14 |
| Participants | #4b | Settings and locations where the data were collected | Cover letter |
| Interventions | #5 | The experimental and control interventions for each group with sufficient details to allow replication, including how and when they were actually administered | sDocument 1. 15-16 |
| Outcomes | #6a | Completely defined prespecified primary and secondary outcome measures, including how and when they were assessed | sDocument 1. 16, 19 |
| Outcomes | #6b | Any changes to trial outcomes after the trial commenced, with reasons | NA |
| Sample size | #7a | How sample size was determined. | sDocument 1. 14–15 |
| Sample size | #7b | When applicable, explanation of any interim analyses and stopping guidelines | NA |
| Randomization - Sequence generation | #8a | Method used to generate the random allocation sequence. | sDocument 1. 17–18 |
|  |  |  |  |
| Randomization - Sequence generation | #8b | Type of randomization; details of any restriction (such as blocking and block size) | sDocument 1. 17–18 |
|  |  |  |  |
| Randomization - Allocation concealment mechanism | #9 | Mechanism used to implement the random allocation sequence (such as sequentially numbered containers), describing any steps taken to conceal the sequence until interventions were assigned | sDocument 1. 17–18 |
| Randomization - Implementation | #10 | Who generated the allocation sequence, who enrolled participants, and who assigned participants to interventions | sDocument 1. 17–18 |
| Blinding | #11a | If done, who was blinded after assignment to interventions (for example, participants, care providers, those assessing outcomes) and how. | sDocument 1. 17–18 |
| Blinding | #11b | If relevant, description of the similarity of interventions | sDocument 1. 17–18 |
| Statistical methods | #12a | Statistical methods used to compare groups for primary and secondary outcomes | 11–12 |
| Statistical methods | #12b | Methods for additional analyses, such as subgroup analyses and adjusted analyses | 11–12 |
| **Results** |  |  |  |
| Participant flow diagram (strongly recommended) | #13a | For each group, the numbers of participants who were randomly assigned, received intended treatment, and were analysed for the primary outcome | 12 |
| Participant flow | #13b | For each group, losses and exclusions after randomization, together with reason | sDocument 4. 8 |
| Recruitment | #14a | Dates defining the periods of recruitment and follow-up | 7 |
| Recruitment | #14b | Why the trial ended or was stopped | NA |
| Baseline data | #15 | A table showing baseline demographic and clinical characteristics for each group | sDocument 4.  2–3 |
| Numbers analysed | #16 | For each group, number of participants (denominator) included in each analysis and whether the analysis was by original assigned groups | sDocument 4.  8 |
| Outcomes and estimation | #17a | For each primary and secondary outcome, results for each group, and the estimated effect size and its precision (such as 95% confidence interval) | 12–14 |
| Outcomes and estimation | #17b | For binary outcomes, presentation of both absolute and relative effect sizes is recommended | NA |
| Ancillary analyses | #18 | Results of any other analyses performed, including subgroup analyses and adjusted analyses, distinguishing pre-specified from exploratory | 12–14 |
| Harms | #19 | All important harms or unintended effects in each group (For specific guidance see CONSORT for harms) | NA |
| **Discussion** |  |  |  |
| Limitations | #20 | Trial limitations, addressing sources of potential bias, imprecision, and, if relevant, multiplicity of analyses | 22 |
| Generalisability | #21 | Generalisability (external validity, applicability) of the trial findings | 19 |
| Interpretation | #22 | Interpretation consistent with results, balancing benefits and harms, and considering other relevant evidence | 20–22 |
| Registration | #23 | Registration number and name of trial registry | Cover letter |
| **Other information** |  |  |  |
| Interpretation | #22 | Interpretation consistent with results, balancing benefits and harms, and considering other relevant evidence | NA |
| Registration | #23 | Registration number and name of trial registry | Cover letter |
| Protocol | #24 | Where the full trial protocol can be accessed, if available | sDocument 1. |
| Funding | #25 | Sources of funding and other support (such as supply of drugs), role of funders | Cover letter |
